#### Phase 3 (quantitative analysis)

The collected data will be analyzed using descriptive statistics (such as frequency, frequency percentage, mean, and standard deviation) and inferential statistics in SPSS ver16. Generalized mixed models of analysis of variance for repeated measures will be used to compare the differences between the values obtained before the intervention and 1 and 3 months after the intervention in each group. We will also calculate the differences in means between the independent groups, as well as their respective 95% confidence intervals. All tests will be run with a 0.05 significance level (*p* 0.05). The Kolmogorov-Smirnov test will be used to determine the data’s normality.

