**Methods:**

Women aged 18–48 years that refer to Tehran Municipality Health Houses will be invited to join the study. Recruitment will continue until a sample of 150 women participants. The study will be conducted using a mixed-methods protocol in three phases. In the first phase, women’s educational and learning needs about STIs will be identified using a qualitative approach. In the second phase, the results from the qualitative approach will be used to design a training program based on an ISD model. The educational intervention will be performed in the third phase. Participants will be randomly allocated into two groups: (1) the intervention group and (2) the control group. Data will be collected using STI Four-Scale of Preventive Behaviors at baseline, immediately, 1-month, and 3-month follow-up assessments. The impact of the intervention on the promotion of preventive behaviors from STIs will then be evaluated.

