### Hypothesis

The main aim is to assess the impact of an educational program based on the ISD model on improving preventive behaviors for STIs Iranian women. Intervention effects will be examined at 4 months. The research hypotheses are as follows:The intervention group will show higher preventive behaviors for STIs than the control group measured by mean scores.The intervention group will show STI knowledge more than the control group measured by mean scores.The intervention group will show STI vulnerability than the control group measured by mean scores.The intervention group will show STI prevention self-efficacy more than the control group measured by mean scores.The intervention group will show STI prevention intentions more than the control group measured by mean scores.

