### Outcome measures

The initial research questions addressed in this study are “Does the educational intervention based on Instructional System Design (ISD) model affect STI preventive behaviors among Iranian women?”. To answer this main question following primary outcomes are expected:Determining and comparing the effects of an educational intervention designed based on the ISD model in STI knowledge among women in the target and control groups before, immediately one month, and three months after the interventions.Determining and comparing the effects of an educational intervention designed based on the ISD model in STI vulnerability among women in the target and control groups before, immediately, one month, and three months after the interventions.Determining and comparing the effects of an educational intervention designed based on the ISD model in STI prevention self-efficacy among women in the target and control groups before, immediately, one month, and three months after the interventions.Determining and comparing the effects of an educational intervention designed based on the ISD model in STI prevention intentions among the target and control groups before, immediately, 1 month, and 3 months after the interventions.

Consequently, we expect the effect of our educational intervention on preventive action regarding STIs among women. To assess the expected secondary outcomes a self-reported assessment addressing preventive actions (using a condom, doing pap-test and genital examination) will be conducted.

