### Instructional System Design (ISD) model steps

#### The ISD includes 10 steps

Identify instructional goalsThe first stage determined what learners could accomplish after completing the educational process [37]. These objectives are the result of need assessments. Need assessments are analyses of the gap between one’s current status and one’s desired status.Conduct instructional analysisWhen learners have achieved their instructional goals, what they should do is determined by stages in a hierarchy.Analyze learners and contextsIn this stage, we will analyze learners’ STI learning experience, preferences, traits, and learning situations.Write performance objectivesWhen students complete the education program, they develop a detailed action plan based on the knowledge they have gained, which is aligned with performance objectives.Develop assessment instrumentsAssessment tools determine whether or not students met their objectives.Develop instructional strategyThe researcher determines the educational method that learners will use to achieve their ultimate learning goals during the educational strategy phase.Develop instructional materialsThe researcher will choose educational materials at this stage based on the instructional strategy.Design and conduct formative evaluationAt this stage, the educational content will be made available to at least 5 to 10 women outside of the research team, and the content’s validity will be evaluated in terms of applicability, comprehensibility, simplicity, and attractiveness.Design and conduct a summative evaluationFollowing the evaluators’ comments in Step 8, any possible and necessary corrections to the educational content will be made.Final evaluationThe effect of the intervention will be evaluated at this stage in three time periods: immediately, 1 month, and 3 months after the end of the educational intervention.

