### The intervention programs

The intervention will be created using the qualitative study’s phase 1 findings. Women who meet the inclusion criteria will be recruited indefinitely until the required sample size is reached. At this point, all participants will be coded and blindly allocated into one of the intervention and control groups by the researchers using a permuted block randomization program: (1) intervention (2) control.

Based on the design of the randomized controlled trial intervention, the impact of the intervention program on promoting women’s STI prevention behaviors will be assessed. Measurements will be taken at baseline, after one month, and after three months of following their respective program, as shown in Fig. 1. In accordance with ethical principles, the participants in the control group will also receive the most effective intervention after the final evaluation and comparisons of the three intervention groups.

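### The named repeated-measures model targets before-after change within each arm and leaves out the immediate assessment, although the trial's questions are intervention versus control

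*Protocol article*

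**What the plan says.** All references are to the protocol article.

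- **The question.** The Hypothesis section states five expectations, each setting intervention against control. The first reads "The intervention group will show higher preventive behaviors for STIs than the control group measured by mean scores". Outcome measures defines the primary outcomes as comparisons, for knowledge for example "among women in the target and control groups before, immediately one month, and three months after the interventions". Sample size and power calculations gives 63 per group, at alpha 0.05 and power 0.80, for a difference between the groups.
- **The analysis.** Phase 3 (quantitative analysis) uses the repeated-measures mixed model to "compare the differences between the values obtained before the intervention and 1 and 3 months after the intervention in each group". It names neither an arm effect nor an arm-by-time term. The next sentence adds "We will also calculate the differences in means between the independent groups", with 95% confidence intervals. It gives no time point and does not say whether the baseline score is used.
- **The assessment times.** The Abstract plans data collection "at baseline, immediately, 1-month, and 3-month follow-up assessments". The final step of the ISD list evaluates the effect "immediately, 1 month, and 3 months after the end of the educational intervention". The intervention programs section says "Measurements will be taken at baseline, after one month, and after three months". The Hypothesis section says "Intervention effects will be examined at 4 months".

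**The concern.** The contrast given to the model is not the one the trial was set up to answer. Change within an arm mixes any effect of the training with everything else that moves a repeated self-report score, such as re-testing and social desirability. Participants and staff are not masked and the outcome is a Likert questionnaire, so some improvement in both arms is plausible. A significant change in one arm and a non-significant one in the other does not show that the arms differ.

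Two further points follow from the same section. The comparison that does answer the hypotheses is tied to no assessment time, and the document names no main time point for it. The model also runs on baseline, 1 and 3 months, while the primary outcomes include a measurement straight after the intervention. An analysis plan written from this section would inherit both problems.

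**Working it through.** **1. What the sample size was built for.** The effect size and SD are not in the text shown, so 63 cannot be reproduced from the document alone. Assume a standardised difference d = 0.5, two-sided alpha 0.05 and power 0.80:

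n = 2(1.960 + 0.842)² / 0.5² = 2 × 7.85 / 0.25 = 62.8, rounded up to 63 per group.

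The stated figure is therefore what a between-group comparison of means gives at d = 0.5. This agrees with the section's own description of the test.

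**2. Assessment times side by side.**

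| Section | Baseline | Immediate | 1 month | 3 months | Other |
|---|---|---|---|---|---|
| Abstract, Methods | yes | yes | yes | yes | |
| Outcome measures | yes | yes | yes | yes | |
| ISD steps, final evaluation | not listed | yes | yes | yes | |
| The intervention programs | yes | no | yes | yes | |
| Phase 3 analysis, mixed model | yes | no | yes | yes | |
| Hypothesis | not listed | no | no | no | 4 months |

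The Discussion adds to the conflict: it speaks of four questionnaire stages and then lists three.

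**3. What within-group testing would do with no true arm difference.** Assumptions: 63 per arm, pre-post correlation r, both arms shifting by the same δ (in SD units), two-sided paired t test at 0.05 in each arm. The standard error of the mean change is √(2(1 − r)/n). At r = 0.5 this is √(1/63) = 0.126. Let p be the chance that one arm's change is significant. The arms are independent, so the chance that only the intervention arm is significant is p(1 − p).

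| Common shift δ (r = 0.5) | p | Only intervention arm significant |
|---|---|---|
| 0 | 5.0% | 0.050 × 0.950 = 4.8% |
| 0.2 SD | 34.6% | 0.346 × 0.654 = 22.6% |
| 0.3 SD | 65.0% | 0.650 × 0.350 = 22.8% |
| 0.5 SD | 97.4% | 0.974 × 0.026 = 2.5% |

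The product p(1 − p) cannot exceed 25%, so shifts of 0.2 to 0.3 SD lie near the worst case. The row for no shift counts a significant change in either direction. A direct two-sided between-group test would favour the intervention wrongly 2.5% of the time at every δ.

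**4. What the baseline score is worth.** Adjusting for a baseline score with correlation r multiplies the outcome variance by 1 − r², so the effective difference is d/√(1 − r²). Two-sample t power at assumed d = 0.5 and 63 per arm, one assessment time:

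| r | Effective d | Power |
|---|---|---|
| no adjustment | 0.500 | 79.5% |
| 0.3 | 0.524 | 83.1% |
| 0.5 | 0.577 | 89.5% |
| 0.7 | 0.700 | 97.4% |

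**The case against.** The strongest reply is that a valid comparison is already planned. A difference in means between randomised arms, with its confidence interval, is unbiased, holds its nominal error rate and addresses hypotheses framed as mean scores. That is correct. A reader might infer that the trial has no between-group analysis, and the text does not support that inference.

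Other strong readings fail for similar reasons:

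- **That the difference is unadjusted.** The section says neither adjusted nor unadjusted. Only the absence of any stated use of baseline can be claimed, and leaving baseline out would cost precision without making the comparison invalid.
- **That the immediate assessment is never analysed.** Only the model sentence is limited to 1 and 3 months. The between-group sentence has no such limit.
- **That nothing is measured at 4 months.** Follow-up is counted from the end of training. The length of training is not given in the text, and the schedule table and figures are not shown. Four months could mean time from the start of training.
- **That the trial carries a 23% false-positive risk.** This needs a rule that declares success when only one arm changes significantly. The protocol states no such rule.

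It can also be said that a mixed repeated-measures analysis normally carries a between-subject factor, so the sentence may be a clumsy description of comparing the arms' changes. That reading is possible. But the sentence places the comparison within each group, and the next one brings in the between-group difference as something additional, so the within-group reading fits better. Wording that allows both leaves the choice open until the data have been seen.

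**Conclusion.** The point holds as a mismatch between the named model and the trial's questions, together with an unreconciled assessment schedule. The document states the contrast and the time points and contradicts them elsewhere, so this is not detail left to an analysis plan. The planned between-group difference prevents it from being a failure to test the hypotheses. Severity: should be fixed before analysis.

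The size is conditional. At r = 0.5, the chance that only the intervention arm is significant runs from about 2.5% to a ceiling of 25%, depending on the common shift, and it matters only if conclusions rest on the within-group tests. The power gain of about 4 to 18 percentage points (79.5% to between 83.1% and 97.4%) rests on an assumed d of 0.5 and assumed correlations of 0.3 to 0.7. The document gives none of these values.

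**What to change.** Rewrite the model sentence in Phase 3 (quantitative analysis) so that the main analysis is:

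- one mixed model fitted to both arms together, with the immediate, 1-month and 3-month scores as outcome;
- arm, time and arm-by-time as fixed effects, and the baseline score as covariate;
- the adjusted arm difference with 95% confidence interval, reported at a main time point that the sponsor names before analysis (3 months, for example);
- within-group changes reported as descriptive only.

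Then reconcile the assessment times across the Abstract, Hypothesis (including what 4 months is counted from), Outcome measures, the ISD steps, The intervention programs and the Phase 3 analysis.

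The cost is analysis wording only. The model uses scores the trial already plans to collect and needs no additional participants or visits. The one dependency is the immediate assessment: its place in the model assumes that the schedule in the Abstract and Outcome measures is the one being followed.

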### Sample size and power calculations

The sample size we require in the quantitative phase to provide sufficient power was calculated as 63 persons for each group. This sample size was calculated to be adequate at an alpha of 0.05 and a power of .80, to test for a difference between the groups. we considered a potential dropout rate of 30%. According to the formula below, we should start with a recruitment target of 75 participants in each group:

In accordance with this approach, a total of 150 women at risk, aged 18 to 48, from the Tehran Municipality Health House, will be recruited using the inclusion and exclusion criteria listed in Table 1.

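### Four unranked primary scales are each tested at 0.05 with no adjustment or testing order, while the sample size covers one unspecified comparison at 0.05

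*Protocol article*

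**What the plan says.** In the protocol article, Outcome measures poses one main question, whether the educational programme affects preventive behaviours, and continues: "To answer this main question following primary outcomes are expected". Four outcomes follow: STI knowledge, STI vulnerability, prevention self-efficacy and prevention intentions. Each is compared between groups at baseline and three follow-ups; for knowledge the wording is "before, immediately one month, and three months after the interventions". The list of ISD steps repeats the three follow-ups: "in three time periods: immediately, 1 month, and 3 months after the end of the educational intervention". No scale and no follow-up is ranked above the others.

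Phase 3 (quantitative analysis) specifies repeated-measures mixed models to "compare the differences between the values obtained before the intervention and 1 and 3 months after the intervention in each group". It adds: "We will also calculate the differences in means between the independent groups, as well as their respective 95% confidence intervals". On error control it says only: "All tests will be run with a 0.05 significance level".

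Sample size and power calculations gives 63 per group and says: "This sample size was calculated to be adequate at an alpha of 0.05 and a power of .80". It does not say which outcome or time this refers to.

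The Hypothesis section lists five hypotheses: overall preventive behaviours first, then the four scales. It adds: "Intervention effects will be examined at 4 months".

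**The concern.** Four outcomes share primary status for one question, and any of them can be declared positive at the full 0.05. The protocol does not require all four to succeed, set an order among them, or divide the 5%. One nominally significant scale out of four could therefore be reported as showing that the programme works, and the Conclusion section intends to generalise from such a result to all women aged 18 to 48 at risk. The error rate of that claim is not 5%.

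Power has the matching problem. The stated 80% belongs to one test at 0.05. If the four primaries were adjusted later, that figure would no longer describe any one scale.

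**Working it through.** **Inputs from the protocol.** Four primary scales; 0.05 per test; three follow-ups in Outcome measures and in the ISD steps; two follow-ups (1 and 3 months) named in the analysis section; 63 per group; power 0.80; 1:1 allocation.

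**Assumptions.** Two-sided tests; a standardised difference of d = 0.5; between-scale correlations of 0.3 to 0.7. The text reviewed gives no effect size or SD, and the formula that the sample size section points to does not appear in it.

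**1. The plan's own figure.** n per group = 2(z₀.₉₇₅ + z₀.₈₀)²/d² = 2(1.960 + 0.842)²/0.25 = 62.8, so 63. An effect of 0.5 SD therefore gives the stated number for a single two-sided test. This makes 0.5 a reasonable working value, but does not show that the sponsor used it.

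**2. False positive rate, one test per scale.** If independent: 1 − 0.95⁴ = 18.5%, which is 3.7 times 5%. With correlated scales (simulation, 200,000 multivariate normal draws):

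| Between-scale correlation (assumed) | Chance of at least one false positive in 4 tests |
|---|---|
| 0 | 18.5% |
| 0.3 | about 17% |
| 0.5 | about 16% |
| 0.7 | about 13% |
| 0.9 (extreme) | about 9% |

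**3. If each follow-up were also tested separately.** The protocol does not state this, so these are bounds.
- Two follow-ups (8 tests), independent: 1 − 0.95⁸ = 33.7%.
- Three follow-ups (12 tests), independent: 1 − 0.95¹² = 46.0%.
- Twelve tests with between-scale correlation 0.3 to 0.7 and between-time correlation 0.5 to 0.7: about 26% to 39%.

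**4. Power for a given scale at 0.05/4 = 0.0125, with 63 per group and d = 0.5.** Normal approximation: Φ(d√(n/2) − z₀.₉₉₃₇₅) = Φ(2.806 − 2.498) = 62%. Using the t distribution: 61%. Restoring 80% at 0.0125 needs 2(2.498 + 0.842)²/0.25 = 89.2, so 90 evaluable per group.

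**5. Power under Holm if all four scales have d = 0.5** (63 per group, simulation, 200,000 draws):

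| Between-scale correlation (assumed) | At least one scale significant (first Holm step) | Average power per scale |
|---|---|---|
| 0.3 | 93% | 72% |
| 0.5 | 89% | 71% |
| 0.7 | 83% | 70% |

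The t distribution lowers each of these figures by about one percentage point.

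**The case against.** **This belongs in a statistical analysis plan.** A multiplicity procedure is often left to that document, which is not shown. If the protocol were silent, that would settle the matter. But it names four equal primaries and sets every test at 0.05. An analysis plan that adjusted would depart from the second statement, and one that chose a single primary would depart from the first. The objection does not remove the point.

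**Each scale has its own hypothesis.** The Hypothesis section lists the constructs separately, so one could argue for separate 5% claims. Outcome measures, however, ties all four scales to one main question, and that supports treating them as one family.

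**Twelve tests.** A reader might infer that four scales at three follow-ups make 12 primary tests, so that the error rate is 46%. The protocol does not support this. The analysis is a repeated-measures model that may give one group-by-time test per scale, the analysis section names only two follow-ups, and it does not say which mean differences are tested. Independence of repeated measurements on the same women is also unrealistic. The 46% is an upper bound only. This objection stands.

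**The 4-month time point.** A reader might also infer that 4 months matches no scheduled assessment. The follow-ups are counted from the end of training, whereas the 4 months have no stated origin. If training lasts about a month (an assumption), 4 months from its start is the 3-month follow-up. The reference is unclear, but not shown to be wrong.

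**Is one outcome already the deciding one?** The first hypothesis concerns overall preventive behaviours, which might be taken as the main endpoint. Outcome measures does not list that overall score among the primaries. The two sections need to be reconciled, but they do not settle which outcome decides.

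**Conclusion.** The concern holds for four unranked primary scales, each tested at 0.05. With one test per scale, the chance of at least one false positive primary result is 18.5% under independence, and about 13% to 17% at assumed correlations of 0.7 to 0.3. Only near-perfect correlation brings it close to twice the nominal level (about 9% at 0.9). Separate testing at each follow-up would raise it further, but that procedure is not stated.

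The stated 80% power applies to one test at 0.05. At an assumed d = 0.5, a given scale tested at 0.0125 has about 61% power with 63 per group. A reader might take that 61% as the power of Holm's first step. It is not, unless only one scale has an effect: the first step succeeds if any scale passes 0.0125, which happens in about 83% to 93% of trials when all four scales have the assumed effect. All power figures depend on an effect size that the text does not give.

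**What to change.** Settle one of two options by amendment before any group comparison is seen.

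1. **One primary.** Name one score at one scheduled follow-up as the sole primary outcome, tested at 0.05, and make the remaining scales and times secondary. The choice is the sponsor's, but it must be reconciled with the first hypothesis on overall preventive behaviours. The calculated 63 per group is unchanged. The cost is that the other scales lose unadjusted primary status: three of the four, if one of them is chosen.

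2. **Four primaries.** Specify one between-group test per scale at one named follow-up, under Holm at a family-wise 0.05. State that the 80% power does not apply to each scale, and give the effect size. At d = 0.5 and 63 per group, power is about 61% for a given scale at 0.0125, and about 70% to 72% per scale under Holm if all four have that effect. The cost is lower stated power, or about 90 evaluable per group to restore 80% at 0.0125.

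Under either option, state the origin of the 4 months in the Hypothesis section, and say which between-group contrasts from the repeated-measures model are the formal tests. Apart from any increase in sample size, these are wording changes.
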